#### Phase 3 – pilot implementation with feedback and ongoing adaptation

##### Objectives

Implementation and adaptation based on adherence and effects including on PICU related complication rates.

While bundle adaptation will result in some variations, the PICU Liberation bundle is expected to have the following key components (see Fig. 2 and Table 3).

Activities:Implement PICU Liberation “check-ins” - a nurse-led, interdisciplinary rounding checklist - to ensure communication and application of all relevant bundle elements as clinically appropriate. The Plan-Do-Study-Act cycle will be utilised in the delivery of each bundle element, and adaptation will occur based on clinician and family feedback, and feasibility assessment following the initial roll-out to improve usability.Develop and implement a daily goals checklist for use during daily multidisciplinary ward rounds, which will include specific reference and reminders for each relevant bundle element.Provide education and training for PICU staff regarding the Liberation program via various mediums (new staff orientation, online, workshops, nursing education program curricula (theory modules and workbooks), individual bundle element in-services, bedside teaching, videos, breakfast sessions, case studies, simulations). This education will introduce the individual components of the bundle, use of assessment items, and recommendations for clinical actions based on assessment results. While education will be consolidated early in the implementation phase, it will be purposively staggered over all phases to ensure adequate updates and inclusion of new PICU staff. Education will be offered to nursing, medical, and allied health staff. Outreach and education to other hospital departments and services including non-clinical areas will be provided to ensure adequate understanding on downstream effects of PICU Liberation.Develop awareness of the relevance and importance of PICU Liberation program and its role in reducing PICU-acquired complications and improving short- and long-term outcomes.Repeat audits of A2F Bundle compliance, patient outcomes and satisfaction by parents as well as staff satisfaction and wellbeing assessments.Assess a) perceptions from staff about the PICU Liberation program and the implementation process; b) perceived barriers and facilitators to its implementation; c) how PICU Liberation has affected care; d) staff knowledge of key bundle elements and components, and e) perception of staff about the PICU Liberation educational resources. Note that the structural aspects (i.e., relative socioeconomic resources, political norms, policies) and their influence will not form part of this assessment.Continue to dynamically assess barriers and enablers to inform the continuous adaption of the A2F bundle operationalisation to improve the feasibility and implementation success.Focus group interviews with key stakeholder groups (i.e., family members, clinicians and administrative leaders) will be conducted to determine a) perceptions of PICU Liberation and the implementation process; b) perceived barriers and enablers to its implementation; and c) how PICU Liberation has affected care. All interview approaches will be used to maximise involvement, including face-to-face interviews, teleconferenced focused groups, and semi-structured interviews using separate interview guides. Families may be interviewed following exposure to the intervention and patient care experience (i.e., at or after PICU discharge). Clinicians may be interviewed mid-implementation to understand their impressions of the knowledge application process and adapt the implementation procedures if necessary.

Throughout Phase 3, the live reporting of selected compliance measures and patient outcomes will be visible to clinicians to provide motivation and real-time evaluation of current uptake of the A2F Bundle and their impact on the process and patient outcomes. Staff feedback will be proffered to consolidate compliance with PICU Liberation practices via on-the-spot feedback; compliment emails; patient and family narratives, photos, and videos included in weekly all-staff communications. Safety metrics will also be monitored and communicated to staff during this period.

#### Phase 4 - assessment of the feasibility of A2F bundle adaptation and the implement success of the PICU liberation program

##### Objectives

Assess feasibility, adherence, acceptability, and impact of pilot study roll-out including on PICU related complications.

Activities:Assess the feasibility of adapting the A2F bundles in PICU.Measure bundle fidelity (i.e. bundle compliance/adherence), using both quantitative analytic and qualitative methods (Table 2, Table 4). If a low degree of fidelity of certain PICU Liberation bundle elements is present, or concerns regarding fidelity are identified, modifications to the bundle elements will be considered to maintain the bundle integrity and primary objective of the PICU Liberation program, i.e., improve patient outcomes.Compare PICU-related complication rate between from pre- (before period) and post-implementation (intermediate and after periods, refer to Fig. 3).Conduct focus groups to ascertain learnings from the implementation process and gather feedback from PICU staff about successes and areas for improvement to inform further adaptation, if required.

**Table 4 Tab4:** Definitions of PICU Liberation program: Bundle Performance and Daily Goals (adapted from PUN et al.) [16]

Element	Days eligible	Performance in the last 24 h it was documented that the patient received	Performance in the last 24 h it was documented on the daily goal checklist
A	All days	≥ 6 pain assessments using the FLACC assessments [26, 27]	FLACC goal
B1	Only days when patient received continuous or intermittent sedation	A spontaneous awakening trial (SAT) if receiving continuous or intermittent sedative infusions OR sedation target set as “light” in the daily goals	Suitability for SAT if receiving continuous or intermittent sedative infusions OR suitability for sedation goal set as “light”
B2	Only days when patient was on ventilatory support	A spontaneous breathing trial (SBT) if receiving invasive ventilation	Suitability for SBT if receiving invasive ventilation
B3	Only days when patient was on ventilatory support	An extubation assessments if receiving invasive ventilation	Suitability for extubation assessments if receiving invasive ventilation
C	All days	≥ 6 agitation-sedation assessments using the RASS (Richmond Agitation-Sedation Scale [29]	RASS goal
D	All days	≥ 1 delirium assessments using the CAP-D [31]	CAP-D requested
E	Only days when patient was not classed as “lizard – for range of motion activities only”	≥ 1 Mobility activity administered that was higher than range of motion	Mobility goal (Lizard – passive range of motion unless contraindicated; Koala – in bed activities including sitting; Wombat – out of bed activities including transfers; Kangaroo – activities away from bedspace including ambulatory) set
F	Only days when family was present	Family member/carer educated on the PICU Liberation bundle and/or participated in at least one of the following: liberation goal setting, cares, neurodevelopmental or early mobility activity, rounds, plan of care.	Suitability of family inclusion in liberation goal setting, cares, neurodevelopmental or early mobility activity, rounds, plan of care.
G	All days	Nutritional assessment tool used OR weight obtained	Nutritional goal set
H	All days	Tool to help personalise the patient for the clinicians administered OR humanism activity administered	Humanism goal set
Baby Liberation	Only infants	“flower” tool to adapt each bundle element to include developmentally appropriate components	Baby Liberation goals documented

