**Fig. 2 Fig2:**
[figure not shown]
PICUstars bundle elements and educational tools

**Table 2 Tab2:** Instruments and measures used to assess implementation feasibility and success (adapted from PUN et al.) [16]

**Instrument**	**Target population**	**Study phase**	**Outputs**
Empathic 30-AUS questionnaire	Parents of eligible children	From phase 2 onwards	Family engagement and satisfaction
PICU Liberation knowledge and perceptions questionnaire	PICU staff	Phase 2, 3 and 4	Drivers, barriers, knowledge gaps
Organisational readiness questionnaire	PICU staff, organisational leadership teams	Phase 2, 3 and 4	Drivers, barriers, leadership effectiveness, culture and employee morale or satisfaction/meaning making
Daily Goal checklist	PICU staff	Phase 3	Proportion of Liberation goals set
Check-in Audit	PICU staff	Phase 3	Drivers, barriers, knowledge gaps
Measure	**Definition**	**Study Phase**	**Outputs**
Feasibility	≥ 75% bundle compliance (daily goals set) at 1 year	Phase 3	Control charts of bundle compliance
Bundle fidelity (bundle compliance): Compliance with daily patient screening for PICU Liberation program using the daily goals checklist; eligible bundle element performed per patient day	≥ 75% absolute and/or ≥ 25% improvement from baseline compliance rate of checklist completion	Phase 3	Control charts of liberation goals set and bundle element activities performed per eligible patient day
Bundle performance	impact of bundle on process and quality of care (the practices that the bundle was designed to influence)	Phase 3	Complete performance is measured by a patient-day in which every eligible element of the bundle was performed (i.e., 100% of the bundle versus anything less) and “proportional performance” as the percentage of eligible elements a patient received on a given day (i.e., “bundle dose”). This will be measured only if the patient was in the PICU for a full 24 h (Table 4)

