F – Family engagement and empowerment	A family member/significant other was educated on the A2F bundle and/or participated in at least one of the following: rounds; conference; plan of care; or A2F bundle related care	Consumer information material educating family/carers on PICU Liberation bundle including goal setting and execution, family participation in cares, neurodevelopmental and early mobilisation activities and rounds	Instances of • Tools used to ensure family inclusion (e.g. Daily goals chart updated with goals set, likes/dislikes on “getting to know you” form utilised), • Family participation in liberation goal setting, • Family participation in liberation goals activity (education provided on PICU liberation, cares, neurodevelopmental and early mobility activity, rounds, plan of care including baby liberation flower, instances of therapeutic cuddles, instances of trips outside the patient’s room) • Family communication with healthcare providers “have you been kept up to date?” • empathic questionnaire completion/opportunity Number of Questionnaires administered to assess family coping and staff meaning making. Empathic questionnaire results (carers' perception of engagement/inclusion/respect/care)
G – Good Nutrition	Not part of adult A2F	Institutional nutritional checklists - Anthropometric assessments (actual weights rather than estimated weights), nutritional assessments recommended at least weekly, patient specific nutritional goals set. Paediatric growth charts completed. Oral feeding readiness assessments	Instances of • Patient weight assessment and weight estimates • Nutritional goals set, instances of nutritional goals achieved • Nutritional assessment tool used, • Weight obtained, instances of appropriate nutrition delivered (defined as 2/3 of requirements reached enterally or parentally from 48 h post I/V), deconditioning, ICU related weakness, cognition. • Nutrition free days. Referrals to speech pathology Oral feeding readiness assessments Nutrition delivery routes i.e. nasogastric, parenteral Empathic questionnaire results (carers' perception of child’s feeding and nutrition management)

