H – Humanism	Not part of adult A2F	Institutional strategies to identify patients' and families' personal, developmental, and cultural preferences developed - family goals documentation recommended at least second daily.	Instances of • Humanism goals set (inclduing photos printed and displayed at bedside, “getting to know you” form/careplan) • Humanism goals achieved, instances of utilisation of tools to help personalise the patient for the clinicians (e.g. “getting to know you”), • Individualised care/opportunity, number and results of questionnaires administered to measure meaning-making for staff and family coping (control charts). • Family awareness of resources such as children’s book library, photo printing service (and use of same) • Completion of “getting to know you” form Empathic questionnaire results (carers' perception of individualised care; use of care planning etc)
Baby Liberation	Not part of adult A2F	Embedded in all PICU Liberation Bundle elements: Institutional strategies to ensure infant neurodevelopment is optimised – Baby Liberation goals documented on “flower” depicting categories of care such as family engagement, use of breast milk for mouth cares, nesting and swaddling etc.	Instances of Use of baby liberation flower use Use of adjuncts such as “zaky” hands, nesting, swaddling, cuddles Empathic questionnaire results (carers' perception of Baby Liberation programme)
Overall bundle performance	“Complete performance” defined as patient-day in which every eligible element of the bundle was performed (i.e., 100% of the bundle versus anything less) “Proportional performance” defined as percentage of eligible elements a patient received on a given day (i.e., “bundle dose” in %)	Additional performance measures: Target setting (Each morning Liberation targets including SP, RASS, mobility targets are to be set within the multidisciplinary ward round and documented in the PICU clinical information system) Targets reached/adjusted: each afternoon during “check-ins”	Measurement of instances of performance of each bundle element per patient day (only measured if the patient was in PICU for a full 24 h from d3 of PICU stay) Instances of daily goals set/opportunity. Instances of Liberation check-ins completed/opportunity Empathic questionnaire instances/opportunity Empathic questionnaire results (carers' perception of Liberation program and individual elements)

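### Table 4 makes B2 and B3 eligible on every ventilatory-support day but credits them only under invasive ventilation, and Tables 2 and 3 give different scored-day rules

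*Protocol article*

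**What the plan says.** **B2 and B3 (Table 4, under Phase 4).** Both rows define eligible days as "Only days when patient was on ventilatory support". B2 performance is "A spontaneous breathing trial (SBT) if receiving invasive ventilation"; B3 is an extubation assessment under the same condition. The daily-goal column repeats that condition for both rows.

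**Performance measures (Table 2).** Complete performance requires every eligible element on a patient-day, with anything less counted as failure. Proportional performance is the percentage of eligible elements received that day.

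**Scored days.** Table 2 says of bundle performance: "This will be measured only if the patient was in the PICU for a full 24 h". Table 3, in its overall-performance row, says: "only measured if the patient was in PICU for a full 24 h from d3 of PICU stay".

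**G and H.** Table 3 has "nutritional assessments recommended at least weekly" for G and "family goals documentation recommended at least second daily" for H. Table 4 makes both eligible on all days. It credits G for "Nutritional assessment tool used OR weight obtained" and H for "Tool to help personalise the patient for the clinicians administered OR humanism activity administered".

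**Baby Liberation.** The Phase 1 objectives define the programme for infants aged 6 months or less. Table 4 scores it for infants, with no age limit.

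**The concern.** The denominator for B2 and B3 is wider than the numerator. B1 offers an alternative route to credit (a light sedation target); B2 and B3 offer none. Under an all-or-none rule, one element that cannot be met decides the whole day.

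These scores are used. Table 2 charts elements performed per eligible patient-day. Selected compliance measures are shown live to clinicians in Phase 3. The control charts guide education and implementation tactics, and low fidelity of an element in Phase 4 can lead to its modification. If the scoring rule lowers B2 and B3, the unit may respond to an artefact. A change in the mix of ventilatory support between periods would also move the charted rate with no change in practice. It follows that a child who steps down from invasive to non-invasive support could lower the score.

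The two scored-day rules raise a separate problem: they define different sets of patient-days for the same measure.

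**Working it through.** The protocol states no expected or maximum performance rate, so there is no figure to reproduce.

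**1. One non-invasive-only day, literal reading.** Each Table 4 row counts as one element.

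| Patient-day | Eligible | Achievable | Maximum proportional performance |
|---|---|---|---|
| Unsedated non-infant, E and F eligible | A, B2, B3, C, D, E, F, G, H = 9 | 7 | 7/9 = 77.8% |
| Same, E and F not eligible | A, B2, B3, C, D, G, H = 7 | 5 | 5/7 = 71.4% |
| Sedated non-infant (adds B1), E and F eligible | 10 | 8 | 8/10 = 80% |

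Complete performance is 0 in every row.

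**2. Unit-wide cap on complete performance.** If s is the share of scored days on non-invasive support only, and every other day is perfect, the cap is 1 − s. The protocol does not give s; the values below are assumed.

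| s | 5% | 10% | 20% | 30% | 40% |
|---|---|---|---|---|---|
| Cap, literal reading | 95% | 90% | 80% | 70% | 60% |
| Cap, condition means not applicable | 100% | 100% | 100% | 100% | 100% |

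A rise in s from 10% to 20% between periods would lower the literal-reading cap by 10 percentage points.

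**3. Reach into the goals measure.** Table 2 gives the checklist output as the proportion of goals set. If the literal reading also governs the goals column, the ceiling on the mean daily proportion is 1 − s × 2/9. At s = 40% this is 1 − 0.089 = 91.1%. With E and F not eligible on the affected days it is 1 − 0.40 × 2/7 = 88.6%. Both lie above the 75% threshold.

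**4. Scored-day rule and short stays.** The Descriptive statistic analyses section plans a sub-analysis of PICU stays shorter than 48 h, and Table 1 requires at least 24 h.
- Counting 24-hour blocks from admission, day 3 runs from hour 48 to hour 72.
- Counting calendar days with admission as day 1 at clock hour a (0 ≤ a < 24), day 3 ends 72 − a hours after admission, which is always more than 48.

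Either way, a stay under 48 h contains no full day from day 3, so the Table 3 rule scores none. Under the Table 2 rule, counted in 24-hour blocks, each such stay has one scored day.

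**5. Table 3 frequencies against Table 4 thresholds.**
- A and C: fourth-hourly gives 24/4 = 6, and Table 4 requires at least 6. They agree.
- D: daily in both. They agree.
- G: a weekly minimum against daily scoring. A unit doing only the minimum, with no other weight recorded, scores 1/7 = 14.3% of days.
- H: a second-daily minimum against daily scoring. If the minimum documentation were the only creditable activity, the score would be 1/2 = 50% of days. Both G and H would be met on 1/7 × 1/2 = 1/14 = 7.1% of days.

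The G and H rates describe minimum practice and are not upper limits.

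**The case against.** The strongest reply concerns the B2 and B3 wording. In row B1 the conditional clause largely restates the eligibility condition. On that pattern, the clause in B2 and B3 may simply say what ventilatory support means, or make other days not applicable; both give a maximum of 100%. Coding of such days could also sit in a fuller protocol or scoring manual. This makes the milder reading plausible, and it is why the cap is conditional. It does not rescue the table: on the milder reading the eligibility column is too wide as printed, and two analysts could score the same day differently.

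A reader might infer that G and H also cap complete performance well below 100%. The documents do not support that. Both Table 3 frequencies are minimums, so daily performance complies with them too. G accepts a weight as an alternative. H is credited for activities other than the family-goals documentation to which the second-daily minimum applies. What remains is a mismatch between the tables.

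A reader might also infer that the feasibility target is out of reach. That criterion is defined on daily goals set, and no success threshold is attached to complete performance.

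On the remaining items, the day-3 rule excludes days and does not count them as failures, and the under-48-hour sub-analysis is not expressly said to cover bundle performance. Table 4's reference to infants may be shorthand for the Phase 1 age limit. These replies reduce the consequences, but the printed definitions still differ.

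**Conclusion.** The point holds at moderate severity. The B2 and B3 eligibility condition does not match their performance and goal conditions. Read literally, complete performance is impossible on a non-invasive-only day and is capped unit-wide at 1 − s: 95% to 60% for an assumed s of 5% to 40%. The size rests on that assumed share, on the literal reading, and on counting B2 and B3 as separate elements. The documents support no single figure for the ceiling, and there is none if the clause means not applicable.

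The scored-day conflict between Tables 2 and 3 depends on neither s nor the reading of B2 and B3. Under the Table 3 rule, stays under 48 h contribute no bundle-performance days. The G and H frequencies and the Baby Liberation age are smaller inconsistencies that need reconciling. What is at risk is the meaning of the compliance and bundle-dose charts and of decisions taken from them; failure of the stated feasibility criterion has not been shown.

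**What to change.** 1. In Table 4, restrict B2 and B3 eligibility to invasively ventilated days for both the performance and daily-goal columns, or state that other days are scored as not applicable.
2. Use one scored-day rule in Tables 2 and 3, and define how days of stay are counted. If the day-3 rule is kept, say that the under-48-hour sub-analysis cannot include bundle performance.
3. Use one age definition for Baby Liberation in the Phase 1 text and Table 4.
4. Have the clinical group reconcile the G and H entries in Tables 3 and 4. Which frequency is right is for that group to decide; eligible days in Table 4 should then follow it.
5. Re-score rates already charted under the corrected rules, and mark the change on the control charts.

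The cost is edits to three tables, the Phase 1 text if its age definition changes, and the scoring script, plus the re-scoring. No new data collection is foreseen, provided that the type of ventilatory support is recorded by day, which the B2 and B3 definitions already presuppose.

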A – Optimising analgesia	PAD guidelines - pain assessments using a valid and reliable instrument	Institutional analgesia and sedation guidelines • Stepwise introduction of analgesics first in agitated or distressed child • Assessment of pain at least fourth hourly, using the FLACC score [26, 27].	Instances of • FLACC assessments/opportunities • Appropriate stepwise use of pain medication (percentage) • WAT [28] assessments/opportunities • Withdrawal instances Opioid and benzodiazepine use Instances of expressed breast milk and sucrose utilisation for procedural pain relief (number of prescriptions and administration episodes) Empathic questionnaire results (carers' perception of child’s pain management)
B – spontaneous awakening and breathing trials	Guide for spontaneous awakening trial (SAT) if patients is receiving continuous or intermittent sedative infusions Guide for spontaneous breathing trial (SBT) if receiving mechanical ventilation	• Safety screening tool and checklist for SABT adapted for PICU to guide nurse-led SABTs • Safety screening tool and checklist for extubation readiness adapted for PICU to guide nurse enabled extubations	Instances of • SABT screening performed/opportunities, • SABT trials/opportunities, • Extubation assessments/opportunity, • Instances of nurse-enabled extubation/opportunity • Ventilator associated pneumonia • Failed extubations, accidental extubations requiring re-intubation within 1 h • Delay from extubation ready to time of extubation Hours/days without invasive ventilation Empathic questionnaire results (carers' perception of child’s spontaneous awakening and breathing trials)

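### Table 4 scores element B2 on whether a breathing trial was received and ignores the safety screen, so a correctly withheld trial makes complete bundle performance unattainable that day

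*Protocol article*

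**What the plan says.** Table 4 (Phase 4) defines bundle performance row by row. B2 is eligible on "Only days when patient was on ventilatory support", and the performance column gives credit for "A spontaneous breathing trial (SBT) if receiving invasive ventilation". Neither cell refers to a screening result. The separate daily-goal column of the same row credits something else: "Suitability for SBT if receiving invasive ventilation".

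Table 3 (Phase 2), element B, lists a "Safety screening tool and checklist for SABT adapted for PICU to guide nurse-led SABTs". Among its measures it counts "SABT screening performed/opportunities" separately from trials per opportunity.

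Table 2 (Phase 1) turns the rows into scores. "Complete performance is measured by a patient-day in which every eligible element of the bundle was performed", against anything less. Proportional performance, also called the bundle dose, is "the percentage of eligible elements a patient received on a given day".

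Other Table 4 rows carry an exemption or an alternative. Element E is eligible on "Only days when patient was not classed as “lizard – for range of motion activities only" days, F only when family is present, and B1 can be met by a light sedation target instead of an awakening trial. B3 credits an assessment, which can be completed whatever its result.

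**The concern.** The programme provides a screen and a suitability entry, so it expects that on some ventilated days a trial will not be suitable. The B2 performance rule has no place for such a day: it stays in the denominator and can be credited only by doing the trial. A team that screens, documents unsuitability and withholds the trial has used the programme as designed and is still scored as missing an element. The rule also credits any trial received, whatever the screen showed.

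This bears on the measures built from Table 4. Performance of eligible elements per patient-day goes onto control charts (Table 2), control chart rules specify improvement, and education is tailored to the changes seen (Impact measures section). Low fidelity of an element can lead to its modification (Phase 4 activities). The effects of elements and their combinations are also to be estimated. If sicker ventilated children fail the screen more often, they receive a lower recorded dose for identical adherence, and any dose-outcome relation then mixes severity with exposure.

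**Working it through.** The plan states no rate or target for B2, so there is no figure to reproduce. The check applies the Table 4 and Table 2 rules to single days and then finds the highest attainable score.

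**Step 1. Single days, invasively ventilated, all other eligible elements done.**

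| Day | B2 eligible | B2 credited | Complete performance |
|---|---|---|---|
| Screen passed, trial done | yes | yes | yes |
| Screen failed, documented, trial withheld | yes | no | no |
| Screen failed, trial done | yes | yes | yes |

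The first and third rows score the same. The third row follows from the credit rule not depending on the screen; the article does not state it outright.

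**Step 2. Proportional performance on a withheld day.** With n eligible rows the maximum is (n − 1)/n. B1, B2 and B3 are counted separately, as Table 4 lists them.
- Sedated, family present, classed Lizard: A, B1, B2, B3, C, D, F, G, H, so n = 9 and the maximum is 8/9 = 88.9%.
- The same, not Lizard (adds E): n = 10, 9/10 = 90.0%.
- The same, infant (adds Baby Liberation): n = 11, 10/11 = 90.9%.
- Fewest rows (A, B2, B3, C, D, G, H): n = 7, 6/7 = 85.7%.

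**Step 3. Ceiling under perfect adherence.** Let u be the share of scored invasively ventilated days on which the screen is failed and the trial withheld. The article does not give u, so the values below are assumptions. The ceiling for the B2 rate and for complete performance on these days is 1 − u. The ceiling for mean proportional performance with n = 9 is 1 − u/9.

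| u (assumed) | B2 rate and complete performance, at most | Mean proportional performance, at most (n = 9) |
|---|---|---|
| 10% | 90% | 98.9% |
| 20% | 80% | 97.8% |
| 40% | 60% | 95.6% |
| 60% | 40% | 93.3% |

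If, as a further assumption, half of all scored patient-days are invasively ventilated, the unit-wide ceiling for complete performance is 1 − 0.5u: 90%, 80% and 70% for u = 20%, 40% and 60%.

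**Step 4. Drift with case-mix.** Take two months with perfect adherence, one with u = 20% and one with u = 40%. The charted B2 rate falls from 80% to 60% although care has not changed.

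**Step 5. After the change.** If B2 is credited for a documented screen plus a trial when passed, or if documented screen-failed days leave the denominator, perfect adherence scores 100% at any u.

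**The case against.** The strongest defence is that the column records what the patient received. As a measure of exposure it need not ask whether a trial was appropriate, and a dose-response question can call for exposure. Element E's exemption does not prove that the authors intended one for B2. This stands as a reason to keep the raw rate of trials received. It does not make that rate a sound measure of fidelity, because a withheld trial is then indistinguishable from a neglected one.

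Much of the needed information is already collected. Table 3 counts screens and trials separately, and the daily-goal column can credit a held-back child whose suitability was documented. That limits the problem to the performance column and makes the repair cheap. Acuity is also to be monitored as a possible confounder, but monitoring it does not correct the score.

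Several stronger readings are tempting and are not supported:
- A reader might infer that feasibility would be missed. That criterion is at least 75% of daily goals set, which does not depend on trials done. The fidelity threshold is worded as a rate of checklist completion, so it is not shown to be affected either.
- A reader might infer that staff see B2 live and are pushed to bypass the screen. Phase 3 speaks of selected compliance measures without naming B2, and says that safety metrics are monitored too. Display is possible but not stated, and any effect on behaviour is conjecture.
- A reader might treat a trial after a failed screen as a safety event. Table 3 says that the screen guides trials; the protocol contains no such classification.
- The ceilings in the working might be read as estimates. They rest on assumed rates. Table 3 also restricts element performance to full days from day 3 of the stay, so u must refer to those days and may differ from the rate over the whole stay.

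**Conclusion.** The point holds for the performance column of Table 4. For any u above zero, complete performance on invasively ventilated days cannot reach 100% even with perfect adherence; its ceiling is 1 − u. This conclusion holds whatever the true rate, and only the size of the shortfall depends on u. The effect on proportional performance is modest: one element on each affected day (a maximum of 85.7% to 90.9% on that day, with B1 to B3 counted separately), and a few percentage points on average. The fidelity charts and bundle dose therefore reflect severity in part, as well as care. The article states this rule in a table of definitions, so it is not a detail left to another document. It is worth correcting before the performance data are analysed, but it does not undermine the feasibility criterion.

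**What to change.** Reconcile B2 in Table 4 with the screen in Table 3, for scoring only, in one of two ways:

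1. Count B2 as performed when the screen is documented and, if it is passed, a breathing trial is done.
2. Remove days with a documented failed screen from the B2 denominator.

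Report the two components from the measures already in Table 3: screens per opportunity, and trials per passed screen as the trial rate. The raw rate of trials received can stay as a secondary measure.

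The cost is a wording change in one table row and its scoring code. Screening and suitability are already to be recorded. The small downside is that B2 becomes less directly comparable with the adult definition, which the secondary measure addresses. No clinical screening criterion changes.
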